### Participants

#### Sample size

This study is an RCT, the intervention group is the Tai Chi group, and the control groups are walking group and waiting-list group. The reduction of Systolic Blood Pressure (SBP) is set as the primary outcome. According to previous study [31], the mean difference and standard deviation of SBP was − 13.33 ± 46.73, − 12.46 ± 33.37 and 3.37 ± 46.01 for Tai Chi compared with walking and waiting-list control. The sample size was calculated using One-Way analysis of variance, F-Tests with the PASS 15.0 software. The standard deviation is set as 20. A total of 65 participants per arm are needed to achieve a power of 80% at a significant level of 5%. A sample size of 195 participants is required to sufficiently detect a target effect size. Considering a 20% drop-out rate, we intend to enroll a total of 234 participants, with 78 participants in each group.

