### Statistical analysis

The statistical analysis will be carried out using SPSS statistical package (version 25.0). Data will expressed as mean ± standard deviations. All primary and secondary analyses will be analyzed based on intention-to-treat. Missing data will be filled by Last Observation Carry Forward rules. Demographic characteristics and other baseline values will be described using descriptive statistics. Baseline characteristics of participants will be compared using chi-square test for enumeration data and one-way analysis of variance for continuous variables. For the primary outcome, we will run a comparison between Tai Chi group, walking group and waiting list control group to figure out whether exercise is more effective for this condition. We will then run another comparison between Tai Chi group and walking group to figure out whether Tai Chi is more efficacious for hypertension. The above analysis will be performed using the ANCOVA model, age, pre-intervention BP, duration of hypertension, and family history of hypertension will be used as covariate [45]. Difference between the groups was calculated as mean differences or odds ratios alongside with their 95% confidence intervals. Multiple comparisons between the groups will be adjusted according to the Bonferroni correction method. The correlational analysis of BP and endothelial function factors will be conducted using Chi-square test. We will perform subgroup analyses based on whether patients are on antihypertensive medication to separate the effect size of Tai Chi.

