## Discussion

In our previous systematic review of Tai Chi for hypertension, we found high heterogeneity and poor methodological quality in original RCTs [28]. Among the included trials, only a few trials reported the results of follow-up, the long-term effect of Tai Chi is unclear. Based on the above facts, we hypothesized that: Tai Chi is superior to waiting-list control and walking control in regulating BP of patients with essential hypertension. To test the hypothesis, we designed this trial with a waiting-list group as a blank control group, which will provide an untreated comparison for the Tai Chi group to determine whether it is effective. We will use walking with targeted intensity as active-control group. By comparing with the walking group, whether Tai Chi is better than active control in hypertensive patients will be determined. Our previous study found that intervention of Tai Chi for 12–24 weeks could significantly lower SBP and DBP than intervention < 12 weeks and intervention > 24 weeks [28]. Therefore, we planned 12 weeks of intervention period to determine the effect of Tai Chi.

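### Plain Bonferroni for the pairwise comparisons is valid but needlessly conservative with three arms; a closed test, or Holm if there is no gate, holds the same 5%

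*Protocol article*

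**What the plan says.** The Statistical analysis section of the protocol article sets out, for the primary outcome, a comparison across the three arms followed by a comparison of Tai Chi with walking, both by ANCOVA. Group differences are to be given as "mean differences or odds ratios alongside with their 95% confidence intervals". The next sentence reads: "Multiple comparisons between the groups will be adjusted according to the Bonferroni correction method". The section does not say whether the pairwise tests depend on the three-group result, how many comparisons form the Bonferroni family, or whether the intervals are adjusted.

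The Discussion gives the hypothesis as two contrasts: "Tai Chi is superior to waiting-list control and walking control in regulating BP of patients with essential hypertension".

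The Sample size section rests on the three-group test alone: "The sample size was calculated using One-Way analysis of variance, F-Tests with the PASS 15.0 software". It uses a 5% level, 80% power and 65 per arm, and adds: "The standard deviation is set as 20". It makes no allowance for a corrected pairwise level.

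**The concern.** The trial is sized on a three-group test at 5%, but its claims about Tai Chi are pairwise and are to be decided at a stricter level. With three arms that extra strictness is avoidable. Once the three-group test has rejected, at most one pair can still be truly equal, so a single pairwise test at 5% is the only remaining source of false claims. Bonferroni on top of such a gate adds no protection that is needed to hold 5%. Without a gate, Bonferroni does protect, but a step-down version gives the same protection and never rejects less. What is at stake is power for Tai Chi versus waiting list, the comparison that decides whether Tai Chi works at all. There is also a risk that published intervals and declared decisions disagree, depending on which interval is reported.

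**Working it through.** **Inputs (Sample size section).** 65 evaluable per arm, SD 20, level 5%, and the prior-study figures, printed with a leading minus sign, as "13.33 ± 46.73, − 12.46 ± 33.37 and 3.37 ± 46.01 for Tai Chi compared with walking and waiting-list control". I read these as three group changes: Tai Chi −13.33, walking −12.46, waiting list +3.37. Tai Chi minus waiting list is then −13.33 − 3.37 = −16.70, and Tai Chi minus walking is −0.87.

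**The plan's own figure first.** The mean of the three is −22.42/3 = −7.473. The squared deviations sum to 34.30 + 24.87 + 117.58 = 176.75. Cohen's f = √(176.75/3)/20 = 0.384. The noncentral F then needs 23 per arm for 80% power, and 65 per arm gives 99.9%. The stated 65 is therefore not reproduced. At SD 20, 65 per arm gives 80% power for f = 0.224, an effect the article does not state. Two patterns with that f are used below as assumptions:

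- One arm apart by d: f = d√2/(3 × 20), so d = 0.224 × 60/1.414 = 9.5 mmHg.
- Evenly spaced means with range R: f = R/(20√6), so R = 0.224 × 20 × 2.449 = 10.97, or 10.98 mmHg before f is rounded.

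**Error rate, all three means equal** (1,000,000 simulated trials, 65 per arm, pooled variance, any pair rejected):

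| Rule | Familywise error |
|---|---|
| Pairs at 5%, no gate | about 12% |
| Three-group test at 5% as gate, then pairs at 5% | 5.0% |
| Bonferroni over three, no gate | 4.4% |
| Gate plus Bonferroni over three | 4.2% |

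The gate suffices because, with three arms, any two pairwise nulls together imply that all three means are equal, and that is exactly what the three-group test examines. The procedure is therefore a closed test.

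**Power for Tai Chi versus waiting list, 65 per arm** (percent; losses against the closed test in brackets, taken before rounding):

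| Scenario | Gate, pairs at 5% | Gate + Bonferroni/3 | Gate + Bonferroni/2 | Bonferroni/3, no gate |
|---|---|---|---|---|
| Article's means, SD 20 | 99.7 | 99.0 (0.7) | 99.3 (0.3) | 99.0 |
| Evenly spaced, range 10.98, SD 20 | 79.2 | 75.8 (3.5) | 77.8 (1.5) | 76.2 |
| Both exercise arms 9.5 below waiting list, SD 20 | 72.0 | 61.4 (10.5) | 66.0 (5.9) | 61.6 |
| Article's means, SD 33.37 | 76.0 | 66.7 (9.3) | 70.9 (5.1) | 66.9 |
| Article's means, SD 42.48 | 52.5 | 43.0 (9.4) | 47.2 (5.3) | 43.3 |
| Article's means, SD 46.73 | 43.9 | 35.2 (8.7) | 39.0 (4.9) | 35.5 |

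SD 33.37 and 46.73 are the smallest and largest prior-study SDs. SD 42.48 is their root mean square, √((46.73² + 33.37² + 46.01²)/3).

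**Holm without a gate.** In the 9.5 mmHg case, Holm over three gives 64.8% against 61.6% for Bonferroni over three, a gain of about 3 points.

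**Intervals.** Bonferroni decisions match 98.3% intervals for three contrasts (1 − 0.05/3) and 97.5% for two (1 − 0.05/2). For three, the t quantiles on 192 degrees of freedom are 2.415 and 1.972, so the matching interval is 2.415/1.972 = 1.22 times as wide. If ordinary 95% intervals were reported, then in the 9.5 mmHg case 76.9% of them would exclude zero while Bonferroni over three rejects in 61.6%. The two would disagree in about 15% of trials.

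**The case against.** Bonferroni is a valid, prespecified and simple choice, and a condensed article may leave the gate, the family size and the interval adjustment to the full protocol or the analysis plan. That is fair, so the silence on those details is not itself the point. The point is the stated method, which can be bettered at the same error rate.

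Four stronger readings are tempting, and the article does not support them.

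- **Error is spent twice.** The direction is the opposite. Gate plus Bonferroni uses 4.2% of an available 5%, and nothing is inflated.
- **Bonferroni protects nothing.** This would hold only if the three-group test were a gate, and the text never makes it one. Ungated, Bonferroni over three brings the error from about 12% to 4.4%.
- **The loss is a flat 10 points.** That size needs a family of three and either a 9.5 mmHg effect that the article does not state or the prior-study SDs in place of 20. On the article's means with SD 20 it is 0.7 points. That small figure is not much comfort either, because those inputs do not give the stated 80% power.
- **The 95% intervals contradict the decisions.** The article does not say they are unadjusted, and Bonferroni intervals with joint 95% coverage would fit the same words.

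One further limit stands. The gated closed test is not better than ungated Bonferroni in every case. With evenly spaced means, ungated Bonferroni over two gives 80.7% against 79.2%, because the gate sometimes blocks a clear pair. Two comparisons do hold without exception: the gate alone rejects everything that gate plus Bonferroni rejects, and Holm rejects everything that Bonferroni rejects over the same contrasts.

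**Conclusion.** The point holds as one of efficiency and clarity, not validity. Under either reading of the three-group test, a rule exists that keeps familywise error at 5% and rejects at least as much as the planned one: pairs at 5% after the gate, or Holm where there is no gate. For Tai Chi versus waiting list at 65 per arm, Bonferroni over three on top of a gate costs between 0.7 and 10.5 points. The cost is near 10 only under the assumed 9.5 mmHg pattern, about 9 with the prior-study SDs, and about 3 with evenly spaced means. A family of two roughly halves these losses. The figures assume equal arms, a common SD and no covariate adjustment. They also read the prior-study figures as group changes. The interval mismatch is a conditional risk, real only if ordinary 95% intervals are set beside Bonferroni decisions.

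**What to change.** Replace the Bonferroni sentence with: 'Pairwise contrasts are each tested at two-sided 5% only if the three-group ANCOVA test is significant at 5% (closed test, familywise error 5% for three arms).' If no gate is wanted, name the contrasts and apply Holm to them. In either case, label the 95% intervals as not simultaneous. If Bonferroni is kept, state the number of contrasts and report intervals at the matching level (98.3% for three, 97.5% for two).

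The cost is one or two sentences, with no change to data collection or sample size. There are two downsides. Under the gate no pair can be claimed when the three-group test is not significant. Ordinary 95% intervals can also still disagree with the decision: in the 9.5 mmHg case in about 5% of trials under the gate (76.9% against 72.0%) and about 12% under Holm (76.9% against 64.8%).

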Several clinical studies reported that Tai Chi may have some benefits in reducing BP and improving quality of life in hypertensive patients [21–27]. We conducted a systematic review of the existing trials of Tai Chi for essential hypertension [28]. However, we found high heterogeneity and poor methodological quality in these studies, which decreased the liability of evidence. Therefore, we will conduct this randomized controlled trial (RCT) aiming at: first, confirming whether Tai Chi is efficacious for patients with essential hypertension; second, observing the short- and long-term effect of Tai Chi; third, investigating the influence of Tai Chi on endothelial function. In addition, we intend to use 24-h BP measurement to monitor patients’ BP, so as to observe the changes more accurately. In order to provide high quality of evidence, we will conduct this trial in line with Standard Protocol Items: Recommendations for Interventional Trials (SPIRIT) [29] and report our findings in accordance with the Consolidated Standards of Reporting Trial (CONSORT) statement [30]. This clinical trial is registered with an identifier (NCT04267471) at clinicaltrials.gov in February 2020.

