### Outcome measurements

#### Primary outcome

The primary outcome in our study is the change in average 24-h SBP between baseline and 12-week after randomization. Ambulatory blood pressure monitoring (ABPM) will be used to assess the BP level. Participants will wear ABPM kit (Space Labs Medical, ABP Monitor 90,217, Redmond, WA, USA) and maintain their usual activities during the monitoring period, while avoiding strenuous exercise. During a 24-h monitoring period, automatic inflation measurement will be taken every 15 min during daytime (07:00 to 22:59) and every 30 min during night-time (22:59 to 07:00). The 24-h ABPM will be measured at baseline, 12 weeks and 24 weeks after randomization. Participants will be asked to record the time to wake up and go to bed in their self-dairies.

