#### Secondary outcomes

The average 24-h DBP, average SBP and average DBP during the daytime and night-time, BP variability, SBP load and DBP load, circadian rhythm of BP, and morning BP surge measured by ABPM will be considered as secondary outcomes.

Endothelial dysfunction is associated with hypertension and its presence correlates with target organ damage. Furthermore, endothelial dysfunction may be both a cause and a consequence of hypertension [41]. Therefore, the change of serum concentrations of Nitric Oxide (NO), endothelin (ET), thromboxane A2(TXA2), vascular endothelial growth factor (VEGF) will be tested to measure the endothelial function using commercial ELISA kits (Bender Med-Systems, Vienna, Austria). Blood samples of participants will be collected at baseline and 12 weeks after randomization.

Home blood pressure monitoring (HBPM) is a self-monitoring tool that can be incorporated into the care for patients with hypertension. Patients will use automated blood pressure monitors (AND, UA-767PBT; Shenzhen, China) to measure BP at home. HBPM will be conducted according to 2019 Chinese Hypertension League guidelines on home blood pressure monitoring [42] during the whole trial. At baseline, patients will measure BP at home every morning (6:00–9:00) and evening (18:00–21:00), 3 times per measurement for 7 days. During intervention and follow-up, patients will measure BP at home every Monday morning (6:00–9:00) and evening (18,00–21:00), 3 times per measurement [42]. Meanwhile, participants will be asked to record BP value in their self-dairies.

Changes in patients’ health-related quality of life will also be assessed according to the Medical Outcomes Study 36-Item Short Form (SF-36) questionnaire Chinese version [43]. This scale contains eight dimensions (physical function, role physical, bodily pain, general health, vitality, social function, role emotional, mental health) and two summary components (physical and mental), with score from 0 to 100. High scores indicate a better quality of life. SF-36 will be measured at baseline and 12 weeks after randomization.

For participants with antihypertensive medication, they will be asked to record the frequency, dosage and types of medication in their self-dairies.

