Existing studies shows that endothelial dysfunction plays an important role in the development of hypertension [46–48]. Regulating endothelial dysfunction has become a significant therapeutic target of hypertension [41, 46, 49]. Aerobic exercise is found to improve endothelial function in hypertensive patients [50, 51]. We assume that Tai Chi reduce BP by regulating endothelial function. Hence, we will additionally investigate the correlation between Tai Chi and endothelial function. In order to achieve high reliability and reproducibility of the results, we will implement more stringent quality control standards. To improve the baseline consistency of participants, we will strictly follow the inclusion and exclusion criteria for participant enrollment. Before formal intervention, included participants will receive standardized Tai Chi training and qualification assessment by experienced coaches to ensure the standardization of Tai Chi movements. During the intervention, we will use fitness tracker to monitor the heart rate of participants to make sure they achieve the target exercise intensity. As for measurement, researchers, Tai Chi coaches and outcome assessors will be separated during the study period. Allocation of participants will be concealed to outcome assessors and data analysts. All researchers will conduct this trial in accordance with SOP. Monthly quality control assessment will be performed to ensure research quality.

We hope the findings of this trial will provide important insight into application of Tai Chi as an effective and acceptable method for hypertensive patients. Successful completion of this proposed study will also contribute to promotion of Tai Chi in the community in the future.

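### The plan names a chi-square test for the correlation of blood pressure with endothelial markers, although all are continuous and no categories are given

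*Protocol article*

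**What the plan says.** The Statistical analysis section of the protocol article gives one sentence to the link between blood pressure and the endothelial markers: "The correlational analysis of BP and endothelial function factors will be conducted using Chi-square test".

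The variables are defined under Outcome measurements:
- Blood pressure: "The primary outcome in our study is the change in average 24-h SBP between baseline and 12-week after randomization".
- Markers: "the change of serum concentrations of Nitric Oxide (NO), endothelin (ET), thromboxane A2(TXA2), vascular endothelial growth factor (VEGF) will be tested", using commercial ELISA kits, with blood drawn at baseline and at 12 weeks.

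For baseline comparisons, the same Statistical analysis section separates methods by type of variable: "chi-square test for enumeration data and one-way analysis of variance for continuous variables".

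The purpose of the analysis is in the Discussion: "We assume that Tai Chi reduce BP by regulating endothelial function". It continues: "Hence, we will additionally investigate the correlation between Tai Chi and endothelial function". The Background lists a related but distinct aim: "third, investigating the influence of Tai Chi on endothelial function".

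**The concern.** A chi-square test of association works on a table of counts. It asks whether two classifications are independent. It returns neither a correlation coefficient nor a slope, which is what an analysis described as correlational should deliver. To run it usefully here, blood pressure and each of the four markers would first have to be cut into groups, and the article describes no such grouping.

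This is a wrongly stated method rather than a missing detail. The test is named, and an analysis plan that followed the sentence would inherit it. The choice also sits badly with the section's own practice at baseline, where chi-square is kept for counts.

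At stake is the support for the mechanistic hypothesis. The sentence is the only stated analysis that links the markers to blood pressure. Carried out as written, it would give no estimate of the strength of that link, and its p-value would depend on cut-points that could be chosen after the data are seen.

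**Working it through.** The article attaches no target correlation, power or sample size to this analysis, so there is no figure to reproduce. What follows shows how the named test behaves.

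**Inputs from the article (Sample size section).** Required total 195; enrolled 234; drop-out 20%. Expected completers: 234 × 0.80 = 187.2, about 187. The figure 195 is the requirement before inflation, not the number left after a 20% loss.

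**1. Raw continuous values.** With N untied values on each side, the cross-tabulation is N × N with a single 1 in every row and column. Each expected count is 1/N, and the statistic is N(N − 1) whatever the data.
- N = 195: 195 × 194 = 37,830 on 194² = 37,636 degrees of freedom, p = 0.24.
- Two simulated data sets with sample correlations of −0.38 and +0.46 gave this same statistic and p-value.

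In this form the test carries no information on the association.

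**2. After grouping: efficiency.** Assumptions, none of them in the article: bivariate normal variables, both split at the median, true correlation ρ near zero.
- Probability that both values lie above their medians: 1/4 + arcsin(ρ)/(2π).
- Correlation in the resulting 2 × 2 table: (2/π) × arcsin(ρ), close to (2/π)ρ for small ρ.
- Noncentrality is about N(2/π)²ρ² for chi-square, against about Nρ² for a correlation test.
- Ratio: (2/π)² = 4/π² = 0.405.
- 187 completers: 0.405 × 187 = 76.
- All 234: 0.405 × 234 = 95. This is the upper limit, approached if last-observation-carried-forward values are analysed for everyone.

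**3. After grouping: power.** Simulation with 2,000 runs per setting, bivariate normal data, two-sided 5% level. The correlations are assumed. It was run at 195 and 234, not at 187.

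| N | assumed correlation | Pearson test | chi-square, median split |
|---|---|---|---|
| 195 | −0.2 | 0.82 | 0.46 |
| 195 | +0.2 | 0.81 | 0.40 |
| 195 | +0.3 | 0.99 | 0.75 |
| 234 | −0.2 | 0.88 | 0.56 |
| 234 | +0.2 | 0.87 | 0.56 |
| 234 | +0.3 | >0.99 | 0.87 |

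With zero correlation, the median-split test rejected in 5.0% of runs at N = 195 and 8.1% at N = 234. Its power at 234 is therefore somewhat flattered. At an assumed correlation of ±0.2 and N = 195, power falls to roughly half.

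**The case against.** The sentence itself is hard to defend, but several limits on the point are fair.

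- **Third aim.** A reader might infer that chi-square is the planned test for the third aim, especially because the Discussion speaks of correlating Tai Chi with endothelial function. The documents do not support that. The third aim is the influence of Tai Chi on the markers, which is a comparison between groups. The markers are secondary outcomes, and the Statistical analysis section provides for group differences as mean differences or odds ratios with 95% CI. The chi-square sentence names blood pressure and the markers, not the groups. This limit stands.
- **Treatment arm.** A reader might also infer that the analysis is confounded by arm. The article does not say that arms will be pooled without adjustment, and a condensed article may leave adjustment to the analysis plan. The concern is therefore conditional.
- **Cut-points.** An analysis plan could supply them. That would make the test computable, but it would still give no correlation or slope and would still lose information.
- **Direction.** The chi-square statistic has no sign, but a grouped table does show direction. What is lost is the estimate of strength.
- **Magnitude.** The 41% rests on assumptions outside the article, and a table with more categories could lose less. It is an illustration, not a property of this trial.
- **Weight.** The Discussion presents the correlation as an additional investigation. The primary outcome, its ANCOVA and the sample size do not depend on it. This limits the severity.

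**Conclusion.** The point holds in a limited form. The article assigns a test for counts to a correlation between continuous variables and gives no categories. That test cannot estimate the association it is meant to describe, and no choice of cut-points changes this.

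Under the stated assumptions, a double median split keeps about 41% of the information, equivalent to about 76 of 187 completers or 95 of 234. The true loss depends on the grouping and on the distributions, neither of which the article gives.

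The damage is confined to the blood pressure–endothelial association offered in support of the mechanistic hypothesis. The sentence should be corrected, but it does not threaten the trial's main conclusions.

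**What to change.** Replace the sentence with one on the continuous scale, for example: the association between week-12 change in average 24-h SBP and week-12 change in each of NO, ET, TXA2 and VEGF will be estimated by Pearson or Spearman correlation, or by linear regression, with 95% confidence intervals.

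Any of these methods corrects the error. Adjustment for arm and for the baseline values of both variables is preferable. If the arms were pooled without it, treatment effects on blood pressure and on a marker could create an association even where none exists within arms.

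Label the analysis exploratory, and state that an association between the two changes is not evidence of mediation.

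The cost is one sentence, settled before the data are seen. Ambulatory pressure and blood samples are already scheduled at baseline and 12 weeks, so no new data are needed.
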